## **Research protocol: part 1**

### **Project summary**

#### **Introduction**

Music therapy is an evidence-based clinical intervention that has demonstrated efficacy in reducing symptoms like anxiety and depression and in providing neuromodulation that promotes well-being. Few studies evaluate its effectiveness in hospital settings, and the frequency of interventions varies widely, with most interventions being scheduled once per week. Since hospital stays for patients with mental disorders are progressively shorter, it is essential to adapt interventions accordingly and test the effectiveness of music therapy in various frequency schedules.

#### **Materials and Methods**

This project will be a randomized clinical trial with two groups: a high-frequency music therapy intervention group (5 sessions/week) and a low-frequency control group (1 session/week). Patients with mental disorders under in-hospital management will be included in the study. The primary outcomes to be measured will be symptoms on the Depression/Anxiety/Stress Scale (DASS-21), while secondary outcomes will be assessed using a questionnaire for the impact of music therapy sessions on adult patients (CISMA, by its Spanish acronym) and a single question on global life satisfaction.

#### **Key Words:**

Sensory art therapies, Music therapy, Music, Colombia, Depression, Anxiety, Psychological stress, Psychological well-being.

## Rationale & background information

The relationship between music and health has been widely studied (1). It has evolved as a complementary intervention for the treatment of mental illnesses and disorders. The American Music Therapy Association (AMTA) defines music therapy as the clinical and evidence-based use of musical interventions to achieve specific therapeutic goals in the treatment of various physical and psychological disorders (2). That are based on the premise that emotional music influence, cognitive and physical aspects of human well-being, stimulating areas of the brain linked to emotions, memory and behavior (2).

Music therapy, in addition to demonstrating benefits in the general wellbeing of people, has been shown to be used as a complementary therapeutic intervention in the treatment of various physical and mental health conditions (3,4). Its versatility allows it to be applied in different settings, populations and pathologies (5-7).

It has been demonstrated that music therapy produces modulation of neurochemical systems, promoting relaxation and well-being (6). In addition, it promotes neuroplasticity and release of neurotransmitters such as dopamine and serotonin, related to pleasure, motivation and well-being (8). Both passive, and active participation in its creation have shown positive effects on cognitive and psychosocial functioning (5) as well as reducing pain and anxiety (9).

Previous studies support music therapy as an effective non-pharmacological intervention for emotional regulation, significantly reducing symptoms of anxiety and depression in different populations, including patients with chronic diseases such as those on hemodialysis (10), people with dementia (11) and psychiatric patients, highlighting its impact on improving mood and self-expression (12). It has also been reported that the combination with Progressive Muscle Relaxation (PMR) is effective in reducing anxiety, depression and stress in patients with breast cancer and gynecological cancer during chemotherapy, also improving the life satisfaction of these patients (13).

However, although music therapy has demonstrated its effectiveness, important questions remain regarding the optimal frequency and duration of the intervention, especially in patients with mental disorders in hospital treatment.

Most music therapy intervention studies with clinical populations contemplate sessions with a weekly frequency and over a relatively long period of several weeks to months. However, psychiatric hospitalizations are currently much shorter, lasting about 10 to 12 days. For this reason, it is necessary to test music therapy interventions that can be administered for short periods, to be adapted as a complementary treatment to psychiatric hospitalization. To the best of our knowledge there is no evidence on the benefit of music therapy sessions more frequently than once a week in a hospital setting in mental patients.

The aim of the present study was to evaluate the effects of high frequency music therapy (five sessions per week) compared to low frequency (one session per week) in patients with mental disorders. Our hypothesis is that patients receiving higher frequency of sessions might have better effects on symptoms of anxiety, depression, stress, and life satisfaction.

## **Objectives and goals of the study**

### **General Objective:**

- To describe the response to high-intensity music therapy in hospitalized patients at the Montserrat Clinic.

### **Specific Objectives:**

- To describe the sociodemographic and clinical characteristics of patients hospitalized with mental illness at Clínica Montserrat.
- To compare the levels of anxiety, depression, stress, levels of general life satisfaction and perception of the impact of music therapy. Before and after low and high intensity music therapy in patients hospitalized at Clínica Montserrat.
- To explore possible associations between sociodemographic and clinical characteristics of patients and their response to low-intensity versus high-intensity music therapy.

## **Study design**

The study will be a randomized controlled clinical trial. Participants will be randomly assigned in a 1:1 ratio to either the high-frequency music therapy intervention group or the low-frequency control group. Randomization will be performed using random number generation. The high-frequency intervention group will receive five music therapy sessions over one week of inpatient treatment, at a rate of one session per day for five consecutive days. The low-frequency control group will receive one music therapy session in one week of inpatient treatment.

The primary outcome will assess symptoms of depression, anxiety, and stress during inpatient treatment. Secondary outcomes will include the perceived impact of the music therapy session on well-being and self-reported life satisfaction.

## **Participants**

### **Inclusion criteria:**

- Individuals over 18 years of age.

- Psychiatric hospitalization of at least 48 hours at recruitment.
- Pharmacological treatment with medication adjustments in the last two weeks.

#### **Exclusion criteria:**

- Prior participation in music therapy programs.
- Primary hospitalization diagnosis of abstinence syndrome or substance dependence.
- Hospitalization duration exceeding six days at the time of selection.

A total of 106 patients undergoing inpatient treatment are expected to be identified over a 32-day period between August and September 2024. A sample of 91 participants is projected to accept participation and will be randomized to either the high-frequency intervention group or the low-frequency control group.

## **Methodology**

**Study Type:** Randomized clinical trial with a concurrent comparative group.

### **Population and Sample**

**Population:** Patients hospitalized in intermediate or general psychiatry units at Clínica Montserrat.

**Sample Size:** Based on relevant studies, especially that of Cantekin & Tan (2013) on music therapy's impact on stress reduction in hemodialysis patients, the response rate to music therapy is estimated to be significant in stress reduction. Although exact percentages are not provided, a statistically significant reduction in stress scores ( $p < 0.01$ ) suggests considerable patient response. The sample size will be calculated to ensure sufficient power for detecting similar effects.

#### **Inclusion Criteria:**

- Adults 18 years or older at recruitment.
- Patients undergoing pharmacological adjustments within the last two weeks.
- Patients hospitalized for less than 48 hours.

**Exclusion Criteria:**

- Previous participation in music therapy.
- Primary diagnosis of substance withdrawal or dependence.
- Hospitalization duration exceeding six days before the start of the first music therapy session.

**Variables**

Sociodemographic data will be collected, including age, gender, educational level, and clinical information such as hospitalization diagnosis, levels of anxiety, depression, stress, general discomfort, life satisfaction perception, intervention-related data like expectations regarding music therapy, and the weekly intensity of music therapy received.

**Dependent Variables:**

- Intensity of Music Therapy:
  - Low intensity
  - High intensity

**Independent Variables:**

- Distress levels for anxiety symptoms.
- Discomfort levels for depressive symptoms.
- Discomfort levels for stress.
- General discomfort levels.
- Life satisfaction levels.

**Sociodemographic Variables:**

- Age
- Gender
- Educational level

**Clinical Variables:**

- Mental illness diagnosis

- Symptom severity

### **Variables Related to Music Therapy:**

- Expectations of music therapy intervention
- Impact of music therapy
- Weekly intensity of music therapy

### **Safety Considerations**

To mitigate risks associated with scale administration and non-participation in music therapy, at least one healthcare professional will attend each session, alongside a certified music therapist.

Monitoring: Clinical and form-based assessments will be conducted throughout the intervention week, with follow-up the following week by health personnel to monitor for any adverse effects.

## **Data Management and Statistical Analysis**

The sample size will be calculated with a power of 85% and a bilateral significance level of 0.05, aiming to detect a mean difference of 4 between experimental and control groups, with an estimated standard deviation of 5. A minimum sample size of 60 subjects (30 per group) will be targeted, with 35 per group to account for possible dropouts.

Data analysis will use Jamovi software, version 2.6 (2024). Descriptive analysis will characterize the sample, including central tendency and dispersion measures, and the normality of continuous variables will be assessed using the Shapiro-Wilk test. Differences between intervention and control groups will be determined using the Mann-Whitney U test for non-normally distributed data, and correlation analyses will use Spearman's nonparametric test where applicable. The analysis will include evaluations of sociodemographic and initial characterization variables, complemented by a correlation matrix for primary variables and outcomes.

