## **Expected results of the study**

### **1. Contribution to the Advancement of Knowledge**

This study will contribute significantly to the field of music therapy in psychiatric settings, particularly in hospitalized patients with mental health disorders. The observed difference in stress reduction between the high and low frequency groups indicates that the intensity of music therapy may be a key factor in treatment efficacy. The association between positive expectations towards music therapy and greater symptom reduction offers a novel perspective on the importance of the psychological component in non-pharmacological treatments, suggesting that patient predisposition may influence therapeutic outcomes.

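### Three DASS-21 scales are primary with no ranking or success rule, and one sample-size calculation at 0.05 covers an unnamed scale; if any one scale may count, the false-positive risk is about 11 to 14%, not 5%

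*Protocol*

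**What the plan says.** The project summary (Materials and Methods) uses the plural: "The primary outcomes to be measured will be symptoms on the Depression/Anxiety/Stress Scale (DASS-21"). The Study design section uses the singular but lists three constructs: "The primary outcome will assess symptoms of depression, anxiety, and stress during inpatient treatment". Neither place orders them, names a DASS-21 total as primary, or says how many must be significant for the trial to succeed.

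Data Management and Statistical Analysis gives one error level and one calculation: "The sample size will be calculated with a power of 85% and a bilateral significance level of 0.05". The effect to be found is 4 points between the arms, and the SD is put at 5. The recruitment goal follows: "A minimum sample size of 60 subjects (30 per group) will be targeted", raised to 35 in each arm for dropouts. The scale to which the 4 and the 5 belong is not stated. The only between-group test named is Mann-Whitney, for data that are not normally distributed.

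The literature basis under Population and Sample concerns stress alone. It cites "a statistically significant reduction in stress scores" in hemodialysis patients and gives no effect size.

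Expected results, item 1, says: "The observed difference in stress reduction between the high and low frequency groups indicates" that intensity may be a key factor in efficacy. Item 2 says that anxiety and depression improved in both groups.

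**The concern.** A two-sided 0.05 describes the error of one test. With three primary scales and no success rule, the protocol leaves open whether a significant result on any one of them would be reported as a positive trial. Expected results draws its efficacy message from stress alone, which fits an any-one reading. Under that reading, the chance of a positive primary result from an ineffective difference in frequency is well above 5%.

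The stated power has the same gap. It belongs to one outcome at 0.05, and the protocol does not say which. Once the error is controlled across three scales, the planned size may not give 85% for each. The protocol intends to take favourable findings to health policy agencies, so the strength of a lone significant scale matters.

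**Working it through.** **Inputs.** Difference 4, SD 5, two-sided 0.05, power 85%, 30 and 35 per group (Data Management and Statistical Analysis); 1:1 allocation and three primary constructs (Study design); 91 participants projected (Participants). Correlations between the scales are not given, so they are assumed.

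**1. The protocol's own figure.** Standardised difference = 4/5 = 0.8. Normal approximation: n per group = 2 × (1.960 + 1.036)² / 0.8² = 2 × 8.978 / 0.64 = 28.06, so 29. The t-test solution is 29.05, so 30. The stated 30 per group reproduces, and t-test power with 30 is 86.1%. For one endpoint the calculation is correct.

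**2. Error if any one of three counts.** For independent tests, 1 − 0.95³ = 0.1426, or 14.3%. The upper bound is 3 × 0.05 = 15%. For equally correlated normal test statistics (simulation, 1,000,000 draws per value):

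| Assumed correlation | Chance of at least one false positive |
|---|---|
| 0 | 14.3% |
| 0.5 | 12.5% |
| 0.7 | 10.9% |
| 0.9 | 8.4% |

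It exceeds 5% at every value examined.

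**3. Power at the first Holm step.** Holm compares the smallest p-value with 0.05/3 = 0.0167. This is the worst case for a scale, and it applies when the other two are null. With standardised difference 0.8:

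| Per group | t-test | Mann-Whitney, normal data |
|---|---|---|
| 30 | 73% | 70% |
| 35 | 81% | 78% |
| 45 (the 91 projected, split evenly) | 91% | 89% |

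At 0.0167 the t-test needs 38.2, so 39 per group, for 85%.

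**4. Power under Holm if all three scales have the assumed effect.** Later steps use 0.025 and 0.05, so power is higher. Simulated t-test power per scale is about 80 to 83% with 30 per group and 86 to 89% with 35, depending on the correlation.

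**5. Loss applied to the projected 91.** The move from 30 to 35 implies 1 − 30/35 = 14% loss. Applied to 45 per group: 45 × 30/35 = 38.6, so 39. Power at 0.0167 is then about 86% by t-test and about 83% by Mann-Whitney.

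**The case against.** The best counter-argument is that a multiplicity procedure is often left to the statistical analysis plan, which is not shown. That stands for the procedure: its absence from the protocol is not a fault in itself. It does not cover which outcome is primary and which outcome the sample size is for. Those are protocol matters, and here three are named and one unnamed scale is sized.

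Second, the any-one rule is an inference. The 0.05 appears only in the sample-size sentence. A DASS-21 total as sole primary, or a rule requiring all three scales, would carry no inflation. This stands, so the 10.9 to 14.3% is conditional. A reader might infer flatly that the 0.05 error rate fails; the text supports this only under an any-one rule.

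Third, a reader might infer from Expected results that the data had been seen, and that anxiety and depression did not differ between groups. Neither is established. The section opens in the future tense, and tense is mixed throughout the protocol. Reference access dates of October 2024 fall after the August to September 2024 recruitment window, so parts of the text may be late, but that does not show when the outcomes were chosen. Improvement in both groups is a within-group statement and does not rule out a difference between them. Population and Sample also gives stress a prior rationale.

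Fourth, quoting 73% as the power after correction would be too harsh, since it is the worst-case step by t-test with 30 per group. Saying that the projected 91 keeps power above 85% would be too generous: after 14% loss that fails under Mann-Whitney.

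**Conclusion.** The concern holds in conditional form. The protocol names three unranked primary scales without a success rule and sizes the trial for one scale that it does not identify. If each scale is tested at 0.05 and any one suffices, the family-wise error is 14.3% under independence, 12.5% at correlation 0.5 and 10.9% at 0.7, roughly two to three times the stated level. The size depends on the assumed correlations; the direction does not.

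The sample-size arithmetic is not wrong. The 85% simply does not extend to each of three scales with the error controlled. With 30 per group, power per scale under Holm lies between about 73% (only that scale has an effect) and 80 to 83% (all three do) by t-test. With 35 per group the corresponding figures are 81% and 86 to 89%. These assume a standardised difference of 0.8 on each scale that has an effect, normal data and equal groups.

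**What to change.** - In Data Management and Statistical Analysis, state that the three DASS-21 scales are tested between groups with Holm at an overall two-sided 0.05. Name the scale and scoring to which the difference of 4 and the SD of 5 refer.
- A single pre-specified primary (one scale or the total) or an all-three rule would also control the error. An all-three rule needs its own power statement: by normal approximation with 30 per group, power is about 67% with independent scales and 73% at correlation 0.5. Given the wording under Expected results, do not make stress the sole primary unless it is documented that the choice came before any results.
- Restate power for 30, 35 and 45 per group at 0.0167, for the test actually to be used, together with the Holm figures when all three scales have the assumed effect.
- Reword the result-like statements in Expected results, items 1 and 2, as expectations, or record when they were written.

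The cost is mostly wording. There are two real downsides. A stress p-value between 0.017 and 0.05 would no longer count if neither other scale is significant. The stated power also becomes slightly less favourable unless more than the minimum 30 per group are analysed.

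### The only association method the protocol names, a Spearman correlation matrix with no arm term, cannot answer the third specific objective on differential response to low- versus high-intensity therapy

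*Protocol*

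**What the plan says.** Under Specific Objectives, the third aim reads "To explore possible associations between sociodemographic and clinical characteristics of patients and their response to low-intensity versus high-intensity music therapy".

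Data Management and Statistical Analysis is the only analysis text in the protocol. For the comparison of groups it says "Differences between intervention and control groups will be determined using the Mann-Whitney U test for non-normally distributed data". For associations it says "correlation analyses will use Spearman's nonparametric test where applicable", and it adds that the evaluation of sociodemographic and initial variables will be "complemented by a correlation matrix for primary variables and outcomes". It mentions one matrix. It does not say whether the matrix is pooled or split by arm, and it gives no interaction term and no comparison of correlations between arms.

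Under Expected results of the study, the first subsection takes "The association between positive expectations towards music therapy and greater symptom reduction" as a sign that patient predisposition may affect outcome.

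**The concern.** A characteristic can be related to outcome in two ways. It can be prognostic: patients with more of it do better or worse whichever arm they are in. Or it can modify the effect: the difference between five sessions and one depends on it. The third objective names the second. A correlation across patients measures the first, or an undivided mixture of the two.

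Both arms receive music therapy, so an overall association also cannot show response to music therapy as opposed to general prognosis during an admission. If the matrix is used to answer the third objective, ordinary prognostic factors may be presented as identifying who benefits from high frequency. Some genuine modifiers would leave no trace in it.

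**Working it through.** **Step 1. The plan's own figure.** Inputs from Data Management and Statistical Analysis: "power of 85% and a bilateral significance level of 0.05", to "detect a mean difference of 4 between experimental and control groups, with an estimated standard deviation of 5". The normal approximation gives n per arm = 2 × (1.960 + 1.036)² × 5² / 4² = 28.1, so 29. The exact t-test has 84.9% power at 29 per arm and 86.1% at 30. The stated 30 per arm (60 in all) is reproduced. It was set for the comparison of arms, not for interactions.

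**Step 2. What each method flags.** The protocol gives no slopes, so these are assumptions shown as a range. Model: outcome = 0.8 × arm + slope × characteristic + error. The characteristic is standard normal, allocation is 1:1, slopes are in outcome SD per SD of the characteristic, and the within-arm outcome variance averages 1. The 0.8 is the protocol's 4/5. There were 4,000 trials per setting, with two-sided 0.05 throughout. Entries are the share of trials with a significant result at N = 60.

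| Truth | Slopes (low, high) | Pooled Spearman | Interaction test |
|---|---|---|---|
| Prognostic only | 0.3, 0.3 | 53% | 5% |
| Prognostic only | 0.4, 0.4 | 80% | 6% |
| Prognostic only | 0.5, 0.5 | 95% | 5% |
| Opposite slopes | -0.25, 0.25 | 5% | 47% |
| Opposite slopes | -0.4, 0.4 | 4% | 88% |
| Opposite slopes | -0.5, 0.5 | 4% | 98% |

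At the 91 patients projected under Participants, the prognostic-only rows become 72%, 93% and 99.5% for Spearman, and the interaction test stays near 5%. Leaving out the arm difference raises the N = 60 Spearman range to about 62% to 98%.

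**Step 3. A modifier acting in one arm only.** With slopes 0 and 0.5 at N = 60, pooled Spearman is significant in about 38% to 46% of trials, depending on how the arm difference and residual variance are set. The interaction test is significant in about 49% to 51%. With slopes 0 and 0.3 the figures are about 17% to 19% and 19% to 20%. Detection is similar or somewhat lower, but a significant Spearman here looks the same as one from the prognostic-only rows.

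**Step 4. What the replacement can deliver.** For a balanced binary characteristic, the standard error of the interaction is SD × √(16/N).

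- N = 60: 5 × √(16/60) = 2.58. Power for a 4-point interaction is Φ(4/2.58 - 1.96) = 34%.
- N = 70: standard error 2.39, power 39%.
- N = 91: standard error 2.10, power 48%.

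The interaction detectable with 85% power is 2.996 × standard error: 7.7, 7.2 and 6.3 points. For 4 points, N = 16 × (5 × 2.996/4)² = 224.4, so 225 patients. Adjustment for baseline would improve this by an amount the protocol gives no figure for.

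**The case against.** The strongest reply is that the protocol never assigns the matrix to the third objective. It calls it a complement, the objective is only exploratory, and a SAP that is not shown may hold interaction models. This is fair as far as it goes. It does not remove the mismatch, because the protocol does name a method for associations, and that method estimates a different quantity from the one the objective asks about. Exploring lowers the standard of evidence but leaves the question unchanged.

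A second reply is that the matrix may be drawn by arm. The text does not say, and pooled is a reading of it. Two matrices side by side would still not test whether an association differs between arms.

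A third is that the interaction test is itself weak at this size. That is true, and Step 4 shows it. The case for it is that it estimates the right quantity with an honest interval, not that it will find most modifiers.

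Some stronger readings are tempting but not supported:

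- A reader might infer that correlation generally misses modifiers. The 4% to 5% arises because equal and opposite slopes cancel. Step 3 shows a much smaller gap when the factor acts in one arm.
- A reader might object to Spearman for all nominal variables. With two-category gender it is usable and close to Mann-Whitney. Unordered diagnosis is a real difficulty, but the qualifier on Spearman leaves room to exclude it.
- A reader might expect change scores to be correlated with baseline severity, which produces a spurious association. Nothing in the protocol plans this. It is a caution only if response is analysed as change.
- A reader might take the expectations passage as a false claim of differential response. It is hedged, sits outside the methods, concerns a variable listed with the music therapy variables, and asserts no low-versus-high difference.

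**Conclusion.** The point holds in this form. The third specific objective concerns differential response, and the only association method stated has no arm term and compares nothing between arms. On the pooled reading at N = 60, a purely prognostic factor is significant in roughly 53% to 95% of trials for assumed slopes of 0.3 to 0.5, against about 5% for an interaction test. A modifier with opposite slopes goes unseen (about 4%). One acting in a single arm is flagged somewhat less often than, or about as often as, by the interaction test, but cannot be told apart from prognosis.

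The percentages rest on the assumed slopes, a normally distributed characteristic and the pooled reading. The mismatch between question and method depends on none of these. It should be corrected, but it touches an exploratory objective and leaves the primary comparison of arms alone. The documents do not support saying that the method must give a wrong answer in both directions.

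**What to change.** For the third objective, state a linear model of the post-treatment score on arm, baseline score, the characteristic and the arm-by-characteristic interaction. Apply it to a short list of characteristics named in advance, with diagnosis entered as a category. Where the characteristic is baseline severity itself, the arm-by-baseline term is the interaction. Report each interaction estimate with its 95% confidence interval and label it exploratory.

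Keep the correlation matrix as description only. Describe overall associations, including any with expectations, as prognostic, not as differential response or as response to music therapy. If response is to be analysed as change, add a sentence that correlation of change with baseline will not be interpreted.

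The cost is wording, since the variables are already to be collected. The drawback is imprecision: with a balanced binary factor and SD 5, a 4-point interaction has about 34% power at 60 patients and 48% at 91. A non-significant interaction must therefore not be read as evidence that response is uniform.
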